**Methods/Design:**

Sixty eligible obese females, with binge eating disorder, will be randomly allocated to receive 20 sessions of transcranial magnetic stimulation intervention (*n* = 30) or the sham transcranial magnetic stimulation intervention (*n* = 30) scattered 3 days/week. Thirty eligible controls will complete the baseline assessment. The primary outcome (number of binge eating episodes) will be assed at each treatment sessions, and 8 weeks after intervention completion (follow-up). It is hypothesized that mean weekly binge-eating episodes will be reduced in the intervention group, compared to the sham group, and that the effect will be maintained at follow-up.

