### Hypothesis

Primary hypothesis:

The rTMS intervention will lead to the reduction of BE frequency and food craving.

The secondary hypothesesrTMS will promote a reduction in ED psychopathology (BES, TEF-Q, LOCES, BSQ,) and associated psychopathology (DASS-21, UPPS), a reduction of anthropometric measures (BMI, hip-waist circumference ratio) and an improvement in neurocognitive performance (Stroop test, executive functioning battery, particularly the CPT-IP).Following rTMS, plasma leptin and estrogen will be decreased along with cortisol levels and proinflammatory biomarkers (PCR, TNF-alpha, IL-6, IL-10) and that there will be an increase in plasma levels of ghrelin (in participants with >20 % of weight reduction), in levels of PYY and BNDF, as well as other anti-inflammatory biomarkers (adiponectin and IL-2).Participants will show that better inhibitory responses and greater activation in response inhibition regions (e.g. the DLPFC).There will be no differences between groups in prevalence of adverse events and dropout rates.Effects will be maintained at 8-weeks follow-up.

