### Intervention

Following assessment, participants eligible for the study will undergo a preliminary fMRI, followed by 20 sessions of neuronavigated rTMS, one session per day, 3 days/week over approximately 7 weeks. Focal rTMS will be performed using a Neurosoft device and a ‘figure of eight’ coil. Brainscience Neuronavigation will be used to guide the placement of the coil to the target PFC region using a template MRI for all participants. The coil will be placed at a 45° angle to the mid-sagittal line to induce a posterior to anterior current in the underlying neural tissue. For the real treatment condition, stimulation will target the left DLPFC at 110 % of the resting motor threshold. Each session of 10 Hz stimulation will apply 1000 pulses to the left hemisphere, with a duty cycle of 5 s on and 55 s off, for a total stimulation time of 20 min. Sham rTMS treatment will be administered with the same TMS methodology used for real intervention, except for the fact that in the sham condition there is no actual magnetic stimulation. In order to mimic the cutaneous sensation and muscle twitching of rTMS without stimulating the brain, focal electrical stimulation will be used as a sham rTMS condition. To ensure treatment adherence, if rTMS sessions are missed, replacement sessions will be schedule within a week.

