### Sample size and statistical analysis

To detect the change in craving and BE frequency before and after treatment intervention, the following parameters were used to estimate sample size: effect size *f* = 0.31 (supposed to be small), alpha error probability =0.05, power = (1-β error probability) = 0.8, number of groups = 2, number of measurements through the follow-up = 3 and correlation among repeated measurements = 0.5.

Statistical Inferences: Two different types of analyses will be used to evaluate the effectiveness of the rTMS. The first (and standard) method is intention-to-treat (ITT) that assumes that every patient allocated to be intervention actually received it [75]. The other paradigm, CACE estimation method [76, 77] will take into account the compliance status (patient’s adherence to the rTMS).The compliance status is defined here as at least one of 20 session of rTMS; CACE estimation, therefore, provides a realistic effect under non-adherence phenomenon being estimated based on the structural equation modeling. Underlying both paradigms, it will be used growth modeling, which examines the development of individuals on one more outcome variables over the time. In growth modeling (on contrary of repeated ANOVAS), random effects are used to capture individual differences in development. The corrected significance level (Bonferroni) to be adopted due to 32 outcomes will be 0,0015. Such procedure will be carried to avoid false discovered rate due to multiple comparisons. All the statistical inference will be done via Mplus 7.0. In addition, careful fMRI image acquisition and processing will be completed and analyzed taking into consideration the limitations of fMRI studies.

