### Randomization

A simple randomization will be conducted with a 1:1 allocation. A randomization sequence list will be created using the website www.random.org, which offers true random numbers; such randomness comes from atmospheric noise, which for many purposes is better than the pseudo-random number algorithms typically used in computer program. Participants will be randomly assigned following simple randomization sequence to one of the two treatments. Group 1 for active rTMS and group 2 for sham rTMS. Patient allocation will be blinded to all participants and study staff, in exception to the professionals providing the rTMS treatment and one doctorate student, responsible for allocation concealment. The allocation sequence will be concealed and sequentially numbered in dark, sealed and stapled envelopes and locked in a key protected cabinet file. Allocation implementation will occur pre-intervention and between the T.2 and T.3 visits.

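### The secondary hypothesis of no difference in adverse events and dropout has no margin, and a non-significant comparison with 30 per arm cannot support it

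*Protocol article*

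**What the plan says.** The Hypothesis section of the protocol article lists, among the secondary hypotheses: "There will be no differences between groups in prevalence of adverse events and dropout rates". No equivalence or non-inferiority margin is attached, and no event or dropout rates are anticipated.

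The abstract plans 30 patients on rTMS and 30 on sham. Sample size and statistical analysis derives the size for craving and binge-eating frequency only, from "effect size *f* = 0.31 (supposed to be small), alpha error probability =0.05", "power = (1-β error probability) = 0.8" and "number of groups = 2, number of measurements through the follow-up = 3 and correlation among repeated measurements = 0.5". The only level adopted for inference is given in the same section: "The corrected significance level (Bonferroni) to be adopted due to 32 outcomes will be 0,0015". The 32 outcomes are not listed there, and safety is neither included nor exempted.

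The section on rTMS tolerability and safety is descriptive. Tolerability rests on counts of adverse events by type and on dropouts, whether caused by adverse events or by something else. Safety rests on whether serious events occur. No test or interval is named.

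On the comparator, the Intervention section says that "focal electrical stimulation will be used as a sham rTMS condition", to imitate the skin sensation and twitching of real stimulation.

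**The concern.** The efficacy hypotheses in the same list gain support when a null hypothesis is rejected. This one would gain support when a null hypothesis is not rejected. Without a margin, a small sample or a strict significance level makes apparent support more likely, whatever the true excess. A multiplicity correction guards against false claims of benefit; applied to harm, it makes a real excess harder to see.

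At stake is what the trial may say about tolerability. It could report that rTMS and sham did not differ in adverse events or dropout while the data remain compatible with a clinically important excess on rTMS.

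The sham adds a smaller difficulty. Electrical stimulation of the skin can cause local effects of its own, so similar rates of local events in the two arms would not by themselves show that rTMS is well tolerated.

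**Working it through.** **1. The plan's own sample size.** Inputs from Sample size and statistical analysis: f = 0.31, alpha 0.05, power 0.8, 2 groups, m = 3 measurements, correlation 0.5. For the between-groups factor of a repeated-measures ANOVA the noncentrality is f² × N × m / (1 + (m − 1) × 0.5). At N = 60 this is 0.0961 × 60 × 3 / 2 = 8.649, with 1 and 58 degrees of freedom, giving power 0.824. The smallest even N reaching 80% is 58. The planned 60 is therefore reproduced, and it is a size for a continuous outcome. No adverse-event or dropout rate enters it.

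**2. The significance level.** 0.05 / 32 = 0.0015625, stated as 0.0015.

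**3. Power to see an excess of events.** The document gives no event rates, so those below are assumptions chosen to show a range. Method: two-sided Fisher exact test with 30 per arm, summing the binomial probabilities of every pair of counts whose p-value is at or below the level. Two-sided testing is also an assumption. Because the protocol says "A simple randomization will be conducted with a 1:1 allocation", the realised split may not be exactly 30/30.

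| Sham | rTMS | Power at 0.05 | Power at 0.0015 |
|---|---|---|---|
| 10% | 30% | 0.372 | 0.051 |
| 20% | 40% | 0.298 | 0.035 |
| 10% | 40% | 0.705 | 0.214 |
| 20% | 50% | 0.596 | 0.159 |
| 10% | 50% | 0.914 | 0.506 |
| 20% | 60% | 0.851 | 0.420 |
| 10% | 60% | 0.985 | 0.804 |

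At 0.05, a true 20-point excess is missed in 1 − 0.372 = 63% of trials (10% on sham) or 1 − 0.298 = 70% (20% on sham). At 0.0015 it is missed in about 95% or 96%.

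**4. Observed splits that would pass as no difference.**
- At 0.05: 10/30 against 3/30, p = 0.057, a difference of 23 points, Newcombe 95% interval 2 to 42 points.
- At 0.0015: 18/30 against 6/30, p = 0.0033, a difference of 40 points, interval 15 to 59 points.

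**5. What identical observed rates would show.** With equal counts in the two arms, the Newcombe 95% interval for the risk difference is about ±17 points at 3/30, ±20 at 6/30 and ±22 at 9/30. Even perfect agreement would leave an excess of 17 to 22 points unexcluded.

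**6. What a formal claim would need.** As an illustration, assume non-inferiority at one-sided 0.025, 80% power and equal true rates of 10%, 20% or 30%. A 20-point margin needs 36, 63 or 83 per arm; a 10-point margin needs 142, 252 or 330. All exceed 30.

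**The case against.** The strongest reply is that the hypothesis is one expectation in a list of predictions, not a decision rule, and that the actual safety plan is the descriptive section on tolerability and safety. That section already provides counts by event type and dropouts by cause, which is much of what a good safety report needs. This stands, and the fix should build on it. It does not rescue the hypothesis, which asserts more than those counts can show.

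A reader might infer that adverse events and dropout will be tested at 0.0015. The article does not say so. It ties that level to 32 unlisted outcomes, in a paragraph about growth modelling, into which event counts and dropout do not fit naturally. The 0.0015 figures are therefore conditional. A reader might also infer that a non-significant result will be declared confirmation. That is not stated either; it follows only from the form of the hypothesis, which offers no margin or interval as another route to support.

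Nor would the stricter level hide any excess, however large. At 0.0015 the power is 51% for 50% against 10%, and 80% for 60% against 10%. At 0.05, an excess of 40 points would usually be found (85% to 91% in the table).

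The sham point is limited. Electrical stimulation could mask local effects such as scalp discomfort, but nothing in the document suggests that it would mask seizures, and counting by event type lets local effects be seen separately.

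Finally, the analysis plan may settle how safety is tabulated. That would supply missing detail, but the hypothesis as published would still be badly posed.

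**Conclusion.** The point holds as a fault in how the safety hypothesis is posed. A no-difference hypothesis without a margin, in a trial of 30 per arm sized for other outcomes, cannot be supported by a non-significant comparison. At 0.05, power is 37% for 30% against 10% and about 70% for 40% against 10%. If 0.0015 also governs safety, which the article leaves open, these become 5% and 21%.

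The figures rest on assumed event rates, two-sided Fisher tests and an even split. The conclusion does not depend on the 0.0015 level: at 0.05 moderate excesses are still missed more often than not, and identical observed rates would leave an excess of about 20 points unexcluded. The sample size, the primary outcomes and data collection are not affected. What changes is what the trial may conclude about harm, so the wording should be corrected.

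**What to change.** Replace the no-difference hypothesis with an estimation aim, keeping the counts already planned.

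- For each adverse event type, for dropout due to adverse events and for dropout for any reason, report the rate per arm and the risk difference with its 95% confidence interval.
- State that safety comparisons lie outside the 0.0015 rule.
- State that a non-significant difference will not be read as no difference.
- Because the sham stimulates the skin electrically, also report absolute active-arm rates of local events and do not judge tolerability on the contrast alone.

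The cost is wording only: no extra patients, visits or measurements. The downside is that the trial gives up the claim of no difference and can state only the range of excess that the interval does not exclude, which at this sample size will be wide.

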## Methods

### Overview and study design

This is a two-arm, double-blinded, randomized controlled trial (RCT). Sixty obese patients diagnosed with BED will be assigned to either: 1) a 20-session treatment protocol of real rTMS, or 2) a 20-session treatment protocol of sham rTMS. Participants will be evaluated for outcome measures before and after the intervention, with a follow up visit 8 weeks after the end of treatment. In addition, a control group comprising 30 female individuals with no lifetime diagnosis of ED (15 obese individuals without a diagnosis of BED and 15 normal weight healthy individuals) will be recruited and enrolled for baseline comparison (biomarkers, neuropsychological and neuroimaging evaluation). The trial design and study flow are shown graphically in Figs. 1 and 2, in line with the SPIRIT 2013 Statement [56].

**Fig. 1 Fig1:**
[figure not shown]
A summary of the study design and participants flow during the study

**Fig. 2 Fig2:**
[figure not shown]
Consort 2010 Flow Diagram

### Participants

The study will be conducted at a specialized outpatient program for eating disorders (ED) of the Federal University of São Paulo (UNIFESP), Brazil. Participants will be females seeking treatment for their ED or referred by their clinical care providers. Recruitment will also include individuals attending online advertisement, study flyers, and newsletters.

All participants will be informed about the study and asked to sign the informed consent term before any procedure is conducted. Study intervention will be completed in approximately 7 weeks.

### Enrollment

#### Inclusion criteria for randomization

Participants are eligible for randomization if they fulfill the following inclusion criteria:Meet DSM-5 criteria for BED.Age between 18 to 55 years old.Right-handed and able to write, read, and understand all elements of the study.Females.BMI ≥ 35 kg/m^2^ and body weight ≤ 150 kg.Laboratory blood tests (fasting glucose, fasting glucose/insulin ratio, complete blood count, TSH and T4) within normal range at study enrollment. In order to exclude participants with diabetes, fasting glucose levels under 126 mg/dl will be accepted.

#### Inclusion criteria for controls

Control participants are eligible if:BMI between 19 and 24.99 kg/m^2^ for normal weight controls and BMI ≥ 35 kg/m^2^ (and less than 150 kg) for obese controls.Normal menstrual cycle (every 21–35 days) for the past 6 months.Age between 18 to 55 years old.Right-handed and able to write, read, and understand all elements of the study.Females.Laboratory blood tests (fasting glucose, fasting glucose/insulin ratio, complete blood count, TSH and T4) within normal range at study enrollment.

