Abnormalities in the food reward system and BE may be associated with emotional and physiological stress. Cortisol, the primary effector of the hypothalamic-pituitary-adrenal (HPA) axis, may mediate stress-induced eating and play a role in disordered eating [22]. Stress is not only associated with disruption of the HPA axis, but may also sensitize pro-inflammatory responses known to take part in the pathogenesis of several ill-health conditions, including psychiatric disorders and obesity. For instance, the adipose tissue is part of the endocrine and innate immune systems [23]. During the fat storage process, adipose tissue produces inflammatory cytokines, such as C-reactive protein, TNF-alpha and IL-6. Importantly, adiponectin synthesis is reduced in obese individuals [24], and the mechanism that trigger the peripheral inflammation has a cascade effect in the hypothalamus [25], leading to the dysregulation in the physiological responses that maintains the sensitivity to insulin, leptin, ghrelin and peptide tyrosine tyrosine (PYY). Furthermore, stress and inflammation have been implicated in the disruption of synaptic signaling and integrity, a process mediated in part through the inhibition of neurotrophins’ function, in which BDNF is the most extensively characterized [26]. Beyond its importance in neural development and synaptic plasticity, there is evidence [27] indicating that BDNF is also essential for weight control and is involved in both homeostatic and non-homeostatic eating. In animal models [28], BDNF has anorexigenic effects in the hypothalamus.

Ovarian hormones are also involved in regulating food intake. Exacerbation of BE seems to occur when estrogen levels are low (premenstrual phase), and when progesterone levels are high (mid-luteal phase) [29]. Estrogen is mostly produced in the ovaries, but also in the liver, adrenal glands and fat tissue. Together with progesterone, ghrelin, leptin, PYY and BDNF, estrogen has a role in appetite regulation [30]. It is known that hormonal dysregulation, including estrogen, has an impact on mood, body weight and shape satisfaction, and on anxiety symptoms [31]. Further, estrogen has both anti-inflammatory and pro-inflammatory roles in the nervous system [32].

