#### Exclusion criteria

History of head or eye injury or epilepsy.Body metallic implants, pacemaker, claustrophobia and any other contraindication to fMRI or rTMS.Current use of psychotropic drugs (except for antidepressants on a stable dose for at least one month).Current use of any anti-obesity drug (e.g. sibutramine, orlistat) and medications that are known to reduce weight, such as Liraglutide and Topiramate (three months washout period for any medication).Pregnant or breastfeeding.Diabetes Mellitus diagnosis.Major psychiatric disorder requiring immediate treatment (e.g. Schizophrenia, Bipolar Disorder).Substance dependence (smokers of less than 5 cigarettes/day will be included).Individuals currently receiving any psychological therapy for ED.Cushing’s and Turner’s syndrome.

*Control participants will be excluded if they meet psychiatric disorder criteria based on the MINI International Neuropsychiatric Interview 7.0 [57].

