##### Clinical measures

Medication use and menstrual status will be assessed based on a questionnaire developed by the authors.

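### Only controls must have regular menstrual cycles, so the baseline comparison of ovarian and related biomarkers between BED participants and controls is at risk of confounding by menstrual status

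*Protocol article*

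**What the plan says.** Under Inclusion criteria for controls, the protocol article requires a "Normal menstrual cycle (every 21–35 days) for the past 6 months". The list covers both kinds of control, 15 obese and 15 normal weight. Under Inclusion criteria for randomization, BED participants have the same age rule ("Age between 18 to 55 years old") but no cycle criterion, and the Exclusion criteria add none.

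Overview and study design gives the purpose of the 30 controls: they "will be recruited and enrolled for baseline comparison (biomarkers, neuropsychological and neuroimaging evaluation"). The Biomarkers section lists estradiol and progesterone with leptin, ghrelin, PYY, BDNF, adiponectin and inflammatory markers. The Background links these: "Together with progesterone, ghrelin, leptin, PYY and BDNF, estrogen has a role in appetite regulation". Under Clinical measures, "Medication use and menstrual status will be assessed based on a questionnaire developed by the authors".

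On glucose, the BED list requires "Laboratory blood tests (fasting glucose, fasting glucose/insulin ratio, complete blood count, TSH and T4) within normal range at study enrollment" and then adds: "In order to exclude participants with diabetes, fasting glucose levels under 126 mg/dl will be accepted". The control list has the first requirement without the added sentence.

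**The concern.** A case-control comparison is interpretable when both groups could have been drawn under the same entry rules, apart from the condition studied. Here one rule differs on ovarian function, and ovarian hormones are among the quantities compared. A BED participant aged up to 55 may have irregular cycles or none, including after menopause. A control may not.

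A difference in estradiol or progesterone between the groups could then reflect the entry rule rather than BED. The Background also ties estrogen to appetite hormones, BDNF and inflammation, so the same could hold, less directly, for those markers. The obese controls, who share the BMI threshold of 35 kg/m² with the BED group, are the contrast that can separate BED from obesity. A mismatch in cycle status weakens that separation for the biomarkers.

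**Working it through.** **Entry rules side by side (protocol article, Enrollment)**

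| Rule | BED participants | Controls |
|---|---|---|
| Age | 18–55 | 18–55 |
| Cycle of 21–35 days for 6 months | not required | required |
| Laboratory panel within normal range | required | required |
| Sentence accepting fasting glucose under 126 mg/dl | present | absent |
| Diabetes excluded | yes (common list) | yes (common list) |
| Stable antidepressant allowed | yes (common list) | yes (common list) |
| Any MINI psychiatric disorder excluded | no | yes |

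The cycle rule is the difference that acts directly on measured biomarkers.

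**Size of the possible bias**

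The article states no figure to reproduce here.

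- From the article: 60 BED participants, 30 controls, of whom 15 are obese.
- Assumed, not in the article: the share *p* of BED women without regular cycles (10–40%) and their mean difference *D* on a marker from regularly cycling women (0.5–1 SD).

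Spurious shift = *p* × *D*. It runs from 0.10 × 0.5 = 0.05 SD to 0.40 × 1 = 0.40 SD.

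Standard error in SD units = √(1/n₁ + 1/n₂):

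- against the obese controls, √(1/60 + 1/15) = 0.289
- against all controls, √(1/60 + 1/30) = 0.224

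With no true BED effect, the unadjusted rejection rate at a two-sided 5% level is P(|Z + shift/SE| > 1.96):

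| *p* | *D* (SD) | Shift (SD) | 60 v 15 obese | 60 v 30 |
|---|---|---|---|---|
| 10% | 0.5 | 0.05 | 5.3% | 5.6% |
| 10% | 1 | 0.10 | 6.4% | 7.3% |
| 20% | 0.5 | 0.10 | 6.4% | 7.3% |
| 20% | 1 | 0.20 | 10.7% | 14.5% |
| 30% | 0.5 | 0.15 | 8.1% | 10.3% |
| 30% | 1 | 0.30 | 18.0% | 26.9% |
| 40% | 0.5 | 0.20 | 10.7% | 14.5% |
| 40% | 1 | 0.40 | 28.3% | 43.2% |

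The 60 v 15 column is the relevant one, because the pooled 30 controls also differ from the BED group in BMI.

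**Precision after restriction**

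If 30% of BED women were set aside (an assumption), 60 × 0.70 = 42 remain:

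- 42 v 30: √(1/42 + 1/30) = 0.239, up from 0.224, about 7%
- 42 v 15: √(1/42 + 1/15) = 0.301, up from 0.289, about 4%

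**The case against.** The strongest case on the other side has four parts.

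*The analysis may handle it.* Menstrual status is recorded, the article is condensed, and a plan not shown may restrict or adjust. This stands against saying that the comparison is confounded; the text supports only a risk. It does not remove the point, because the one-sided entry rule is fixed in the protocol itself. The absence of a stated adjustment is not the complaint.

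*The figures are assumed.* That is so. At 10% and 0.5 SD the inflation is negligible. The common exclusions (pregnancy, breastfeeding, Cushing's and Turner's syndromes, abnormal thyroid tests) also remove some causes of absent or irregular cycles. If the corrected level of 0.0015 in Sample size and statistical analysis covers these comparisons, which the article does not make explicit, the same calculation for 60 v 15 gives about 0.2–3.7%. That is still above 0.15%, but small in absolute terms.

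*The scope is limited.* This stands fully. The entry rules are the same for both randomised arms.

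*Restriction changes the population.* The restricted BED group is not the whole randomised sample. However, a menstrual-status indicator in a full-sample model leads to nearly the same place. All controls cycle regularly, so the indicator absorbs the non-regular BED women and the group contrast is drawn from the regularly cycling ones.

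A reader might also infer three further faults that the documents do not support:

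- *That BED participants need not have normal glucose.* Both lists require the same panel within normal range, and diabetes is excluded for all. The 126 mg/dl sentence may simply state the accepted limit. At most it opens a non-diabetic band of unstated width.
- *That antidepressant rules differ by group.* The stable-dose exception is in the common list. What differs is that "Control participants will be excluded if they meet psychiatric disorder criteria", a rule about diagnosis. That difference is real but says nothing about menstrual status.
- *That menstrual status should be a covariate in the randomised analysis.* Nothing in this mismatch bears on rTMS versus sham.

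**Conclusion.** The point holds for the menstrual criterion. Regular cycles are required of controls only, and the baseline comparison for which controls are enrolled includes hormones that depend on cycling. The comparison is therefore at risk of confounding by menstrual status, most directly for estradiol and progesterone and less directly for the related biomarkers.

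Against the 15 obese controls the false-positive rate would be about 5–28% at a nominal 5%. This rests wholly on an assumed 10–40% share of BED women without regular cycles and an assumed 0.5–1 SD difference. The lower end is harmless and the upper end is not; the document cannot say which applies. The rTMS-versus-sham comparison and both primary outcomes are untouched.

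The glucose wording is a minor matter of consistency, not evidence of metabolic confounding.

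**What to change.** State that the baseline biomarker comparison with controls, and above all with the obese controls, is made among BED participants who meet the controls' own cycle criterion (21–35 days for the past 6 months), classified from the menstrual status already recorded. Report alongside it the full-sample comparison adjusted for menstrual status and age. Fix this before the biomarker data are examined.

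Separately, reconcile the two fasting-glucose statements in the BED inclusion list with each other and with the control list, so that it is clear whether one limit applies to both groups.

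The cost is analysis wording, with no new data and no change to the randomised trial. The downside is the small loss of precision worked out above. The restricted result would also describe regularly cycling women with BED rather than the whole BED sample, and the report should say so.
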